### Vaginal pharmacokinetics of MB66 film in Rhesus macaques

Macaques were dosed once, or once daily for three consecutive days with  $\frac{1}{2}$  of an MB66 film thus each dose containing 5 mg of VRC01-N and 5 mg of HSV8-N. The film was inserted via a small speculum. At intervals after dosing, pre-weighed Tear Flo filter paper strips were applied to the deep, mid and superficial vagina, and reweighed to determine the sample weight. Antibody levels of diluted samples were determine by ELISA with HIV gp 120 or HSV-2 gD antigen coated wells. [Figure 5](#) plots antibody levels for both mAbs at intervals after a single dose of  $\frac{1}{2}$  film and

Figure 6 at intervals after three consecutive daily doses of  $\frac{1}{2}$  film, timed after the third dose. During the study some animals were menstruating, and mAb levels were lower and dropped faster in these animals. Vaginal residence half life in non-menstruating animals was between 4 and 8 hours.

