**Effect of sampling procedures on film retention and antibody levels:** Other aspects of our procedure are recognized to also have some potential for depletion of vaginal mAb levels. The speculum required to obtain localized samples from multiple sites has the potential to remove antibody or partially hydrated film. We will attempt to minimize this by removing adherent film or fluid from the speculum with a wooden tongue depressor and tip the speculum to maximize vaginal retention of fluid during speculum withdrawal.

**CVL sampling and timing:** CVL sampling is required for assessments for which Tear Flo sampling gives inadequate volumes, namely for viral neutralization studies and immune mediators. CVL sampling will be delayed until after Tear Flo sampling has been completed at the 24 h post dosing time point, a time when data adequate to calculate the vaginal retention kinetics from the 1, 4, and 24 hours Tear Flo sampling without interference from CVL sampling, has already been obtained. An estimate of the amount of film inadvertently removed, if any, will be recorded.

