## 10.3 ADMINISTRATION

A study clinician will manually insert the MB66 film in the clinic for Segment A participants, and Segment B participants will self-administer their first dose of study film in clinic in the presence of the study clinician (to assure themselves and study staff of their ability to insert the film), and then self-administer doses 2-7 at home. Segment B participants will take home their remaining doses in a vial capped with a Medication Event Monitoring System (MEMS) cap, to provide objective data about adherence with and timing of at home dosing, (each opening of the MEMS cap will be electronically recorded for time and date, with data downloaded at Visit 4). An extra dose of study film will be available for each Segment A participant in case of an

initially unsuccessful insertion, and three extra doses provided for each Segment B participant in case of unsuccessful insertion in clinic, at home, or for the possibility of delaying Visit 4 to Day 8 instead of Day 7. *(While the intended duration of exposure for Segment B participants is 7 days, participants who are only able to reschedule Visit 4 on Day 8 post MB66 administration will be allowed to do so. For that group, the total dosing will be 8 days rather than 7. Every effort will be made to bring participants back on Day 7 so as to minimize variation in product exposure. Participants will only be enrolled if they indicate their availability to return on Day 7, but if a scheduling conflict should arise post enrollment, they will be allowed to return to the clinic for Visit 4 on Day 8 after administering an additional dose of film on day 7.)*

For Segment A participants the study will be open label (unmasked). For Segment B, the film identity (active or placebo) will be randomly assigned and assignment will be single blinded (study film identity will be masked to the participants) Reliable blinding of study staff will not be feasible due to the non-identical degree of film translucency of the active and placebo films.

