#### 11.1.1.4 Segment A, Visit 3: Follow-Up Visit Day 1, PK sampling

This visit will assess safety endpoints and adverse events, and obtain vaginal Tear Flo samples to determine residence half-life and vaginal distribution of the study MABs, and a blood sample to determine the level of systemic absorption of the study MABs. [Table 8](#) outlines procedures that will be conducted in Visit 3. All vaginal sampling (swabs, Tear Flo and CVL) is conducted via speculum. At all visits where CVLs are taken, the CVL will be performed *after Tear Flo sampling*. As with Tear Flo sampling, the actual time of CVL sampling will be recorded in this and in all CVL sampling in other visits in Segment A and B.

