#### 11.1.2.4 Segment B, Visit 3: Follow-up Day 1 with PK Sampling

This visit will assess safety endpoints and adverse events, obtain vaginal Tear Flo samples to determine study Mab concentrations and vaginal distribution of the study MABs, and obtain a blood sample to determine the level of systemic absorption of the study MABs, and perform other testing as outlined in [Table 12](#). All vaginal sampling (swabs, Tear Flo strips, and CVL) will be performed via speculum. The participant will be given eight doses (thus including two extra

doses) of the study product to be administered at home within a container capped with a MEMS cap to provide an electronic record of opening for disbursing each dose. Testing of the proper functioning of the MEMS cap device will be performed, and instructions for its use will be reviewed, including cautioning against “curiosity openings”, and cautioning against removal of more than one film at a time. Participants will be reminded of the need for storage at controlled room temperature, and to avoid high temperature exposures outside the home, for example leaving the films in a vehicle. Instructions on film insertion will be reiterated, and participants will be asked if they have questions about film insertion and if they wish to do further training with the pelvic models.

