#### **11.1.2.6 Segment B, Visit 4: Follow-up Visit Day 7)**

The Visit 4 target date for Segment B is Day 7. The window for the visit also includes Day 8. Consequently, some participants will receive 8 daily doses although every effort will be made to schedule participants for Day 7. When Visit 4 is scheduled, participants will be instructed to insert film on the day before the visit at the same time as the visit is scheduled on the following day, to allow sampling at 24 (+/-4) hours after the last daily dose. During the visit participants will return any unused films, be interviewed for AEs, evaluated for safety endpoints by pelvic exam, and pharmacokinetic sampling of blood and vaginal Tear Flo samples and CVL will be obtained to assess MAb levels and distribution. CVL will also be assayed for antiviral activity, and immune mediators. Additional samples will be used to assess vaginal pH, Nugent score, and microbiome by PCR. All vaginal sampling (swabs, Tear Flo strips, and CVL) will be performed via speculum. Observations on the acceptability of the MB66 study film will be obtained in Segment B participants after they have completed seven daily insertions of the film. Participants will complete a computer assisted structured interview (CASI). We recognize the limitations of acceptability endpoints in participants who have not used the product during intercourse, but expect to learn important new information regarding their experience inserting the film, the degree of vaginal discharge with this product format, and their attitudes toward antibody based products and the plant based manufacturing system. Visit 4 procedures are detailed in [Table 13](#) below.

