#### **14.7.3 Secondary Endpoint Analysis**

Summary statistics of frequencies, percentages, and 95% confidence intervals will be provided for categorical data. Means, standard deviations, medians, ranges and 95% confidence intervals will be provided for continuous data. Methods for the analyses of the secondary endpoints are described below. This Pre-Phase I study may not have an adequate sample size to detect significant differences within or between treatment arms.

In general, for continuous measures that are collected at multiple time points (vaginal and systemic antibody levels), repeated measures mixed models will be fit that allow the individual women to be considered as random effects in the models. Whenever possible the actual time of the measurement will be recorded during the study and the actual time interval between measures (i.e. number of hours between measures) can be considered in the repeated measures mixed models for accounting for time. This will allow for potentially a more sensitive analysis to the impact of time between measures to take place since there may be some variability among participants in the timing of the assessments. These models will be exploratory, but will allow longitudinal comparisons to be made both within treatment group and between treatment groups. For categorical or binary outcomes measured at multiple time points (film dissolution) a generalized estimating equations (GEE) approach will be used to compare participants within and between groups. As stated above, these analyses will be considered as primarily exploratory since there will be a limited sample size. If measures are taken only at one post randomization time point then we can compare groups using 2-sample t-tests (for continuous variables) and Fisher's exact tests (for categorical variables).

If the continuous data collected does not follow a normal distribution then appropriate transformations (i.e. log transformation) will be considered and if these do not fix the problem then non-parametric approaches will be considered (i.e. Kruskal Wallis tests).

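### Section 14.7.3 times the antibody models by hours between samples, not hours since the last film, so in Segment B a time slope would make daily dosing seem to lengthen residence

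*Protocol*

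**What the plan says.** Section 14.7.3 plans repeated measures mixed models, with women as random effects, for continuous measures taken at several times, naming vaginal and systemic antibody levels. To use actual rather than nominal times, it offers one scale: "the actual time interval between measures (i.e. number of hours between measures) can be considered in the repeated measures mixed models". The reason given is that assessment times may vary among participants. On status it says: "These models will be exploratory, but will allow longitudinal comparisons to be made both within treatment group and between treatment groups". Dose time is not mentioned.

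Other sections supply the timing:

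- Section 11.1.2.6 asks Segment B women to insert the last film the day before Visit 4, "to allow sampling at 24 (+/-4) hours after the last daily dose".
- Section 10.3 says of home dosing that "each opening of the MEMS cap will be electronically recorded for time and date".
- Section 6.2.2 delays the lavage until after the 24 h strips, when there will be "data adequate to calculate the vaginal retention kinetics from the 1, 4, and 24 hours Tear Flo sampling without interference from CVL sampling".
- Section 11.1.1.4 (Segment A, Day 1) aims to "obtain vaginal Tear Flo samples to determine residence half-life and vaginal distribution of the study MABs". The matching Segment B text in section 11.1.2.4 aims to "obtain vaginal Tear Flo samples to determine study Mab concentrations and vaginal distribution of the study MABs" and does not name half-life.
- Section 6.3, third hypothesis, expects daily administration to lengthen residence time relative to a single film.

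**The concern.** After a single film, elapsed time and time since dose are the same clock apart from a constant, so either works in Segment A. In Segment B they separate. The home films go in between the Day 1 and Day 7-8 samples. The Day 1 and Visit 4 samples are both troughs about 24 h after a film and should read much alike, yet on the named scale they lie about 144 h apart. A line through them reads near-equal levels as very slow loss of antibody.

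The error favours a stated hypothesis. Vaginal concentration is a secondary endpoint, and the models are meant to support comparisons within and between groups. If Segment B looks more persistent only because of its time axis, the third hypothesis gains support it has not earned.

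The same scale also cannot adjust for when the last film was actually inserted. That drives the Visit 4 level directly.

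**Working it through.** The protocol states no half-life estimate or bias for these models, so there is no figure of its own to reproduce. The check asks what one log-linear slope would return on each clock when true decay is identical throughout.

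**Inputs**
- True half-life h of 4, 6 or 8 h. The range is from section 6.1.3, macaque film data: "Vaginal residence half life in non-menstruating animals was between 4 and 8 hours". Its use for women is an assumption.
- Starting level 10 mg/mL, the expected pre-coital concentration in section 6.2.1.
- Seven daily films at 0, 24, ..., 144 h.
- Post-dose strips at 1, 4, 24, 168 and 336 h after the first film (Days 0, 1, 7 and 14). Hours since the last film are 1, 4, 24, 24 and 192, since 168 − 144 = 24 and 336 − 144 = 192.
- My assumptions: first-order decay, additive doses, one least-squares line on log concentration, no noise.

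**Formulas**
- C(t) = sum over earlier doses d of 10 × 2^(−(t − d)/h)
- Apparent half-life = −ln 2 / slope

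**Step 1: the two troughs.** The Day 1 level is 10 × 2^(−24/h): 0.156, 0.625 and 1.250 mg/mL for h = 4, 6 and 8. At Day 7, superposition multiplies this by about 1/(1 − 2^(−24/h)), that is 1.016, 1.067 and 1.143, giving 0.159, 0.667 and 1.429 mg/mL. Even with unchanged decay, the later trough is slightly higher than the earlier one.

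**Step 2: fitted half-life in Segment B (h)**

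| Samples and clock | h = 4 | h = 6 | h = 8 |
|---|---|---|---|
| 1, 4, 24 h only | 4.0 | 6.0 | 8.0 |
| To Day 7, elapsed time | 38 | 59 | 83 |
| To Day 7, literal gaps 1, 3, 20, 144 h | 33 | 51 | 72 |
| To Day 7, time since last film | 4.0 | 6.1 | 8.3 |
| To Day 14, elapsed time | 7.9 | 11.9 | 16.0 |
| To Day 14, time since last film | 4.0 | 6.0 | 8.1 |

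To Day 7, elapsed time overstates half-life 9.5, 9.8 and 10.4 times. With the scheduled Day 14 sample the excess is about two-fold (7.9/4, 11.9/6, 16.0/8).

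**Step 3: an assay floor.** The noise-free Day 14 levels are far too low to measure, so I repeated the fit with values floored at 50 ng/mL. That is the limit quoted in section 6.1.3 for the animal serum ELISA; applying it to vaginal fluid is an assumption. Elapsed time then gives about 22 h in Segment B for every h. Time since last film gives 11 to 12 h, so part of the excess comes from the floor, not the clock. Segment A (1, 4, 24, 168 h) with the same floor gives about 10 h. The Segment B to Segment A contrast is therefore again about two-fold (22/10), although true decay is the same.

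**Step 4: timing within the Visit 4 window.** From 20 to 28 h is 8 h, so the level changes by 2^(8/h): 2^(8/8) = 2-fold and 2^(8/4) = 4-fold between the extremes.

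**The case against.** The strongest reply is that the protocol does not fix the model tested above. The wording is permissive, the models are labelled exploratory, and nothing says that time enters as one straight line rather than as visit categories. Section 14.7.2 leaves further detail to a separate SAP, which is not at hand and may settle the matter. All of this stands, and it limits the weight of the point. What remains is that the protocol names one scale for actual time, that this scale does not suit one of its two segments, and that no dose-anchored alternative is offered.

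A reader might infer that the trial will report a Segment B half-life about ten times too long. The documents do not support that. Half-life is not a named output of these models, and the 1, 4 and 24 h samples that section 6.2.2 assigns to retention kinetics return the true value. The ten-fold figure also requires leaving out the scheduled Day 14 sample. However, in Segment B those early samples all follow the first film, since home films are dispensed at the Day 1 visit. They cannot test whether repeated dosing lengthens residence; that needs the Visit 4 and Visit 5 samples, where the named scale fails.

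On last-film timing, women are told to insert it at the clock time of the next day's visit, and the safety call repeats this. Most intervals should therefore lie well inside the window, and the 2- to 4-fold range is the extreme, not the typical spread.

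**Conclusion.** The point holds as a modest flaw in the stated time scale. A time slope or time-by-segment contrast on hours between measures would make daily dosing appear to lengthen residence when decay is unchanged. The size is about two-fold over the full Segment B schedule, and up to about ten-fold only if data stop at Day 7. These figures rest on first-order decay, a half-life carried over from macaques, a single log-linear slope and no noise. A model with visit as a category would not show the slope error, but it would still not adjust for variation in last-film time.

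It should not be read as showing that the single-dose retention kinetics are wrong, or that the primary safety analysis is touched. The size applies to vaginal levels. I have none for serum, because the protocol gives no serum half-life to work from.

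**What to change.** In section 14.7.3, replace hours between measures with hours since the most recent dose:

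- for the 1, 4 and 24 h samples, from the insertion time in clinic;
- for the Visit 4 and Visit 5 samples, from the last MEMS opening.

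Add dosing occasion (after the first dose versus after repeated dosing) as a fixed factor. Read it against the 1.02- to 1.14-fold rise in trough that accumulation alone would produce under the assumptions above.

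The cost is a few words in the protocol and the SAP. Section 11.1.1.3 already requires actual Tear Flo sampling times in both segments and the insertion time in Segment A, and the MEMS cap logs home openings. For Segment B, the clinic insertion time is implied by the 1 h and 4 h sampling, so confirm that the case report form captures it. The one real drawback is that a MEMS opening is a proxy: it shows when the vial was opened, not when the film was inserted.

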#### **14.7.4 Exploratory Endpoint Analysis**

##### Introduction

Given the small sample size (n~30), and the preclinical nature of this research, comparisons between the active and placebo products are not the primary aim of this study. However, we will compute the effect sizes for all of the comparisons between formulations to provide guidance for outcomes interpretation and for future studies. While we do not expect many comparisons between active and placebo products to be statistically significant in this study, we do anticipate that some comparisons may be statistically significant, and in either case provide useful data for planning follow-up efficacy studies.

##### Ex vivo antiviral effect

One-way analysis of variance and Kruskal Wallis tests will be used, where appropriate, to evaluate differences in the antiviral activity in CVL between MB66 and placebo arm. In addition, analysis of covariance (ANCOVA) models will be considered when comparing groups. These models would include the baseline HSV seropositivity as a covariate in the models since there may be an imbalance between groups on this pre-treatment characteristic.

##### Cervicovaginal microbial environment

Vaginal pH: Vaginal pH levels will be compared between groups using two-sample t-tests. Pre- to post-exposure shifts will be analyzed with a longitudinal mixed model.

Nugent score: Differences in the categorized Nugent score at each visit and between the MB66 and placebo arms will be evaluated using chi-square tests, while McNemar's tests will be used to evaluate pre- to post-exposure shifts between normal (score 0-3) and abnormal (score 4-10) vaginal microflora within each treatment arm and from baseline (Visit 2, pre-exposure) to Visit 4 (one week post initiation of dosing). Any shift from normal at baseline to intermediate or Bacterial Vaginosis at Visit 4 will be considered a meaningful change in vaginal flora.

Vaginal microbiome assessment: Samples will be stored frozen for later analysis for the prevalence of microorganisms determined by polymerase chain reaction (PCR) for bacterial ribosomal DNA. The prevalent microorganisms will be compared between the MB66 and placebo arms using Fisher's exact tests, while pre- to post-exposure shifts will be evaluated within each group using McNemar's tests. Prevalence of microorganisms determined by polymerase chain reaction (PCR) for bacterial ribosomal DNA (as the percent of total identified organisms) will be compared between the MB66 and placebo arms using 2 sample t-test if distribution is normal (and after log transformation if not normal). Pre- to post-exposure shifts will be analyzed with a longitudinal mixed model (log transformed if not normally distributed).

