### **7.3 EXPLORATORY OBJECTIVES**

- To assess the antiviral effect of the MB66 antibodies *ex vivo* in cervicovaginal lavage fluid from participants after dosing with MB66 film
- To compare the effects of MB66 and placebo films on the cervicovaginal microbial environment using pH, Nugent score, and bacterial ribosomal DNA PCR
- To compare the effect of MB66 and placebo films on cervicovaginal immune mediators by Luminex and ELISA assays
- To assess the acceptability of the MB66 vaginal film after 7 days of use

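### The flora shifts the protocol calls meaningful are never compared between MB66 and placebo: the binary shift tests are McNemar tests within each arm (minor, exploratory endpoint)

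*Protocol*

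**What the plan says.** Section 7.3 states the aim as a comparison of products: "To compare the effects of MB66 and placebo films on the cervicovaginal microbial environment using pH, Nugent score, and bacterial ribosomal DNA PCR".

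Section 14.7.4 gives two analyses for the Nugent score. Between arms: "Differences in the categorized Nugent score at each visit and between the MB66 and placebo arms will be evaluated using chi-square tests". For change over time, taken from Visit 2 (pre-exposure) to Visit 4: "McNemar's tests will be used to evaluate pre- to post-exposure shifts between normal (score 0-3) and abnormal (score 4-10) vaginal microflora within each treatment arm". It then defines the event of interest: "Any shift from normal at baseline to intermediate or Bacterial Vaginosis at Visit 4 will be considered a meaningful change in vaginal flora".

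For the microbiome, Section 14.7.4 plans a between-arm test of organisms ("The prevalent microorganisms will be compared between the MB66 and placebo arms using Fisher's exact tests") and, for binary change, "pre- to post-exposure shifts will be evaluated within each group using McNemar's tests". Organisms expressed as a percentage of the total are compared between arms by t-test, and "Pre- to post-exposure shifts will be analyzed with a longitudinal mixed model (log transformed if not normally distributed"); no arm contrast is stated for that model. Section 14.4.3 defines the meaningful microbiome change as a move from a lactobacillus-dominated community to a mixed one dominated by BV-associated bacteria.

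**The concern.** The objective is between arms, and the defined event is one-directional and conditional on being normal at baseline. McNemar within an arm matches neither. Its null hypothesis is that worsenings and recoveries are equally frequent in that arm. Two features of this trial make the mismatch matter.

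- **Shifts common to both arms.** Between Visit 2 and Visit 4 both arms have repeated speculum sampling, a Day 1 lavage (5 mL of buffered saline dispensed three times, Section 11.5.2) and a week of film vehicle. Section 14.3 justifies the placebo as the means of separating vehicle from antibody effects. A within-arm test does not use it.
- **Recoveries.** Exclusion criterion 19 in Section 9.3 bars recent symptomatic bacterial vaginosis, so women with intermediate flora or asymptomatic BV can enrol. In McNemar's test, such a woman returning to normal offsets a woman who moved the other way.

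The visit-level chi-square is between arms, but it compares prevalence at a visit and does not ask which women moved. The event that the protocol itself singles out therefore has no planned between-arm comparison. At stake is how an exploratory signal on flora is read and carried into later studies.

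**Working it through.** **Inputs.** From the protocol: 15 evaluable women per arm in Segment B (Section 8.4.2); two-sided 5% level (stated in Section 14.3 for the Fisher comparison of AE2 rates, assumed here for flora). Assumed, because the protocol gives no flora rates: proportion normal at baseline π = 0.70 to 0.80; proportion s of normal women who shift; proportion r of abnormal women who recover.

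**The plan's nearest figure.** The protocol states no power for flora. Table 18 uses the same sample size and Fisher's test. Exact enumeration over two Binomial(15, p) arms gives 89.0%, 83.8-83.9%, 88.0-88.1% and 87.2%, against the stated 88%, 83%, 88% and 87%. The method reproduces the plan's figures to within 1 point.

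**Step 1: two within-arm tests are not a comparison.** Exact McNemar with b worsenings and no recoveries has two-sided p = 2 × 0.5^b.

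- MB66, b = 6: p = 2/64 = 0.031.
- Placebo, b = 5: p = 2/32 = 0.0625.
- If 12 women per arm were normal at baseline, the comparison of the shift is 6/12 versus 5/12: Fisher p = 1.00.

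One arm is significant and the other is not, with no evidence of a difference.

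**Step 2: false signal in the active arm.** Suppose MB66 has no effect, normal women shift at rate s in both arms, and nobody recovers. McNemar rejects when at least 6 of 15 worsen, so the probability is P(Bin(15, πs) ≥ 6).

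| Common shift s | π = 0.70 | π = 0.80 |
|---|---|---|
| 20% | 1.2% | 2.3% |
| 30% | 7.5% | 12.7% |
| 40% | 22.2% | 33.9% |

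Recoveries lower these figures: at s = 40% with 40% recovering they are 6.3% and 15.0%. Fisher's test among baseline-normal women rejects about 3% of the time at s = 40%.

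**Step 3: power for a real effect.** Take s = 50% on MB66 and 5% on placebo. The probability of being abnormal at Visit 4 is πs + (1 − π)(1 − r). For π = 0.70 and r = 0, that is 0.35 + 0.30 = 0.65 on MB66 and 0.035 + 0.30 = 0.335 on placebo. Power was enumerated exactly; the chi-square is normal versus abnormal, without continuity correction.

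| Recoveries among baseline-abnormal women | Planned chi-square at Visit 4 | McNemar, MB66 arm | Fisher, baseline-normal women |
|---|---|---|---|
| None | 40-52% | 44-60% | 55-65% |
| Half, both arms | 46-60% | 10-24% | 55-65% |
| Half, MB66 only | 14-32% | 10-24% | 55-65% |

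Ranges run from π = 0.70 to π = 0.80. Fisher's test does not depend on r because baseline-abnormal women are not in it.

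**The case against.** The strongest reply is that the flora objective is already served between arms. The Nugent sentence opens with a between-arm test at each visit, and the microbiome has Fisher tests, t-tests and a mixed model. Under randomisation the Visit 4 comparison is a valid test of an MB66 effect on prevalence without any conditioning on baseline. When recovery is equal in both arms, it gives up only about 5 to 9 points of power to the Fisher comparison (46-60% against 55-65%). All of this stands.

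Three stronger readings are tempting and not supported. A reader might infer that flora is tested only by McNemar; the planned between-arm tests and mixed model contradict that. A reader might infer that the plan is likely to report false harm; rejection rates above 20% need about 40% of normal women to shift from common causes within a week. Nothing in the protocol suggests that rate, McNemar is also run on placebo, and no text says that significance in the MB66 arm will be attributed to MB66. A reader might also infer that recoveries would hide real harm; for the planned chi-square that needs recovery to be more frequent on MB66 than on placebo.

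It is also fair that Section 14.7.4 says between-product comparisons are not the primary aim, and that Section 14.7.2 leaves further detail to a statistical analysis plan. What survives is narrower. The protocol does name the tests for the binary shifts, and it names within-arm ones. The effect sizes promised for between-formulation comparisons attach to no planned comparison of the defined shift.

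**Conclusion.** The point holds in limited form. The two changes defined as meaningful (Nugent normal to intermediate or BV, and lactobacillus-dominated to BV-associated) are not themselves compared between randomised arms. The tests assigned to the binary shifts answer a different question, and setting two within-arm p-values side by side does not repair that. The existing visit-level tests are valid but take no account of baseline status. The cost of that is modest when recovery is similar in both arms and large only when it differs.

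All shift, recovery and baseline rates here are assumptions. The conclusion about which question each test answers does not depend on them; the power and false-signal figures do. Severity is minor: the endpoint is exploratory, the enrolment pause and stopping criteria in Section 13.8 do not use Nugent or PCR results, Section 12.1.1 does not count asymptomatic BV as an adverse event, and the primary safety conclusion is unaffected.

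**What to change.** In Section 14.7.4, add a between-arm analysis of the defined shift. Among women with a Nugent score of 0-3 at Visit 2, compare the proportion with a score of 4-10 at Visit 4 between MB66 and placebo, reporting the difference with an exact confidence interval and Fisher's exact test. Do the same for the categorical microbiome shift defined in Section 14.4.3, among women with a lactobacillus-dominated community at Visit 2. Keep the visit-level between-arm tests, and label the within-arm McNemar results descriptive.

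The change is to analysis wording only; the swabs and smears are already in the schedule. The cost is that baseline-abnormal women do not contribute to this one comparison: 15 × 0.20 = 3 to 15 × 0.30 = 4.5 per arm under the assumption, so about 3 to 5. They remain in the visit-level tests.
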